### Training conditions

The experimental manipulation in this study was within the Training Design of the Training Transfer Conceptual Model [71]. Table 1 highlights key similarities and differences across groups. Trainers were balanced across conditions. Consistent across each training condition was treatment content (i.e., treatment manual, coding manual, and workbook) and consultation with a trainer.

**Table 1 Tab1:** Condition comparison on key design features

Feature	LC	CM	DE
Primary level targeted	Multiple (senior leader, supervisor, clinician)	Clinician	Clinician
Unique features	1. Addressing multiple organizational levels within the organization that might impact implementation,	1. A “top-down,” hierarchical training approach (EBT expert to a community supervisor to trainees within the community clinician’s organization),	1. Broad public health impact,
	2. Organizing “core teams” (i.e., workgroups) within each organization,	2. Strong and specific focus on two trainees who are advanced clinicians, and	2. Easy access to interactive training program online
	3. Emphasizing cross-site sharing among teams,	3. Extensive use of in vivo skill modeling, direct practice, observation and feedback within the clinic setting.	3. Revieing materials is self-paced, independent, and can be repeated
	4. Utilizing a quality improvement process, which focuses on measuring and monitoring incremental improvements		
Ultimate goal	Create a learning organization	Focus on fidelity	Make training accessible
Trainers—number	3 + admin support	2	1
Trainers—expertise	PCIT, Program Development	PCIT	PCIT
Trainees—number per site and role within organization	2–5 members comprise a “core team.” Minimally include clinicians and supervisors.	2 senior clinicians who also treat families	Unlimited
Training group size (approx)	20 participants from 6 agencies	12 participants from 6 agencies	Unlimited
Training components/ structure	Pre-work phase	5-day initial training;	Web-based training + materials
	3 2-day Learning Sessions	2-day training 6 months after the initial training	
	Action periods between learning sessions		
Time in workshop training	6 days	7 days	None
Consultation (group)	2 h per month	2 h per month	2 h per month
Time frame	12 months	12 months	12 months
Training site	Offsite	Offsite	On-site
Videotape review and feedback	Minimum four tapes per trainee by within agency supervisor	Minimum four tapes per trainee by PCIT expert	None

#### Learning collaborative

Consistent with the Institute for Healthcare Improvement [29] and NCTSN [31] protocols, the LC involved three phases: collaborative pre-work, learning sessions, and action periods. Pre-work activities were conducted prior to a face-to-face meeting to ensure that all participants come to the learning session with similar levels of PCIT knowledge. The pre-work “launch phase” (3 months) included readings, material review, and conference calls. Learning sessions included three 2-day, face-to-face meetings over a period of 9 months. Action periods occurred between learning sessions and were characterized by plan-do-study-act cycles, use of improvement data, use of technology to support learning, team meetings, and conference calls. Four people per clinic participated in the LC as part of a “core team,” including an administrator, supervisor, and two clinicians. Each LC included multiple clinic teams, was organized by a coordinator, and supported by faculty experts in PCIT and program development (e.g., financing, marketing, encouraging referrals, mobilizing clinic support). Components that make this training condition unique include the following: (1) addressing multiple organizational levels; (2) organizing “core teams”; (3) emphasizing collaborative, cross-site sharing; and (4) utilizing a quality improvement process focused on collecting implementation targets/data. After 1 year of intensive training, agencies selected one supervisor and one clinician to participate in additional training focused on training others within their organization. The inclusion of within-organization training in the LC is consistent with the intention of the training model to embed local expertise and promote sustainability. Those clinicians not involved in within-organization training continued phone consultation with the trainer at a reduced frequency (once per month) over a 6-month period (months 12 through 18 of training).

#### Cascading model

Consistent with the protocol recommended by the PCIT International Training Committee [85], this condition consisted of 40 hours of initial face-to-face contact with a PCIT trainer, an advanced live training (16 hours ) with real cases 6 months after the initial training, and bi-weekly contact with a trainer conducted over 12 months. After the end of the 12-month intensive training, trainees participated in 6 months of ongoing consultation and training, to begin training others within their organization. Each CM training group included 8 to 12 participants (two clinicians from each organization). Components that make CM unique include the following: (1) a “top-down,” hierarchical training approach; (2) strong and specific focus on two advanced clinicians; (3) extensive use of in vivo skill modeling, direct practice, observation, and feedback within the clinic setting; and (4) capacity for clinicians to return to organization as “in-house” or “within-organization” trainers to replicate clinical training with other clinicians within the organization. CM also focuses on trainers reviewing clinicians' videetaped sessions and providing them with feedback on treatment fidelity and competence. The clinicians trained by “in-house” trainers are also included in the study so that we can understand the impact of a cascading training.

#### Distance education (DE)

An online training similar to TF-CBT Web [86] was developed by the University of California, Davis Medical Center PCIT Team (SAMHSA grant; PI: [name]) and used in this study as part of the DE condition. The online training consisted of 11 modules/training topics, took clinicians approximately 10 hours to complete and included written materials, vignettes, videos, and quizzes for each topic. In this DE condition, the website was augmented for each participant with copies of the PCIT Treatment manual, Dyadic Parent–Child interaction Coding System (DPICS) Manual, and DPICS Workbook. Clinicians also participated in phone consultation with a trainer consistent with other training conditions.

### Outcome measures and assessment procedures

The three primary outcomes of interest are training, implementation, and client outcomes. A review of outcomes measures across participants and timepoints is provided in Table 2.

**Table 2 Tab2:** Assessment measures across timepoints and participants

Construct	Measure	Brief description	Timepoints	Participant(s)	Method
Training outputs					
Knowledge					
	The PCIT Coaches Quiz [96]	22-items to assess clinicians’ knowledge of PCIT concepts and coaching scenarios; mixed question format of multiple choice and short answer	Baseline	Supervisors	Self-report
			12 months	Clinicians	
			24 months		
Skill					
	PCIT Therapist Competency Checklist	17-item checklist of PCIT competency criteria based on established PCIT Training Guidelines	Ongoing	Completed by the trainer on clinicians	Live Behavior observation
	FIRST Coach Coding System [97]	Assesses the quality and style of a therapist’s coaching	Ongoing	Completed by the trainer on clinicians	Video review behavior observation
	Supervisor Impressions of Competence in PCIT [98]	Supervision structure, practice, content, and skill	6 months	Completed by the supervisors on clinicians	Supervisor Report of clinician behavior
			12 months		
			24 months		
Attitude					
	Training Satisfaction [99]	Satisfaction with on-site training materials, content, and trainer	During each on-site training	Supervisors	Self-report
				clinicians	
	Treatment Satisfaction	Satisfaction with the treatment, concerns or barriers to using PCIT, and suggestion for improving its relevance	6 months	Supervisors	Self-report
			12 months	Clinicians	
			24 months		
	Usage Rating Profile—Intervention [100]	35-item measure of intervention usage, including acceptability, understanding, feasibility, and system support	6 months	Supervisors	Self-report
			12 months	Clinicians	
			24 months		
	PCIT Learning Experience Feedback Form	8-item survey to assess satisfaction with PCIT training	6 months	Administrators	Self-report
			12 months		
			24 months		
Training inputs					
Trainee characteristics					
	Demographic Information Form	Basic demographic and contact information	Baseline	Administrators	Self-report
				Supervisors Clinicians	
	Treatment Provider and Practices Survey [101]	Demographic information and variables hypothesized to affect adoption of EBTs	Baseline	Supervisors Clinicians	Self-report
Training design					
	Training Fidelity Checklist	Checklist to ensure that trainers implement the LC and CM conditions in the manner intended (accuracy, consistency)	During each on-site training	Research staff member	Behavior observation/ video review
Training dose					
	Consultation Records	Standardized form completed by the trainer for contact with trainees to document key topics discussed	During each consult call	Completed by the trainer on clinicians	Trainer report
	PCIT Feedback Form	Clinical open-ended feedback provided to clinicians on clinical competency	Ongoing	Completed by the trainer on clinicians	Behavior observation/ video review
Organizational/work environment					
	Infrastructure Survey of Children’s Mental Health [102]	Structured, 1-hour, interview survey to obtain information on the governance, financing, staffing, services, and implementation practices of organizations as well as their perspectives on factors important to the implementation of new treatment and services	Baseline	Administrators	Interview (qualitative and quantitative)
			12 months		
			24 months		
	Dimensions of Organizational Readiness—Revised [103]	21-item scale that requires respondents to rate the importance of specific intra- and extra- organizational variables (e.g., leadership support, fiscal benefits, match, admin burden) likely to affect implementation	Baseline	Administrators	Self-report
			12 months		
			24 months		
	TCU Organizational Readiness for Change Survey [104]	Assessment of organizational functioning including program needs, training needs, and pressures for change, program resources, and organizational dynamics	Baseline	Administrators	Self-report
			12 months	Supervisors	
			24 months		
	TCU Survey of Organizational Functioning [104]	Includes the TCU Organizational Readiness for Change plus nine additional scales assessing job attitudes and workplace practices	Baseline	Administrators	Self-report
			12 months	Supervisors	
			24 months		
Implementation outcomes					
Treatment process and acceptability					
	Treatment Implementation Feedback Form [105]	13-item questionnaire to understand clinicians’ experiences using an EBT including the extent of use, relevance, and helpfulness of the treatment	6 months	Supervisors	Self-report
			12 months	Clinicians	
			24 months		
	Treatment Summary Report [106]	15-item questionnaire to assess nature and outcome of treatment services for a particular family (e.g., service length, barriers, disposition) to provide acceptability data for a specific family	Ongoing as families discharge from treatment	Supervisors	Clinician report and chart review
				Clinicians report on child and family behavior	
Fidelity					
	PCIT Session Fidelity Checklist [107]	Detailed checklists of components of each PCIT session to measure fidelity	Ongoing through video review	Completed by the trainer on clinicians	Behavior observation/ video review
	Use of Treatment Practices [108]	15-item clinician self-report of completion of specific treatment tasks with an individual family	Ongoing as families discharge from treatment	Supervisors	Self-report
				Clinicians	
Cost					
	Chief Financial Officer Survey (updated version of a survey created by Olmstead et al. [109])	Provides information necessary to complete the cost analysis (e.g., program overhead and fringe rates, annual expenditures	Baseline	Administrators	Self-report
Adoption	Time-tracking phone app	Provides time estimates of trainer activity by condition	Ongoing	Trainers	Self-report
	Evidence-Based Practice Survey [110]	List of evidence-based practices respondent has implemented in the last year	Baseline	Administrators	Self-report
			12 months	Supervisors	
			24 months	Clinicians	
Penetration					
	PCIT Learning Experience Feedback Form	Report of consumer levels (e.g., the number of consumers who receive PCIT divided by the number of consumers who were eligible to receive PCIT and did not receive it	6 months	Administrators	Self-report
			12 months		
			24 months		
Sustainability					
	Evidence-based Practice Sustainability Telephone Interview	Survey of current PCIT delivery, penetration, practice adaption, and barriers to sustaining PCIT practice within the organization	24 months	Administrators	Self-report
Family and child outcomes					
Family characteristics					
	Demographic Information	Measure to gather information including age, race, gender, family constellation, living arrangement, school placement, and socio-economic status.	Baseline	Families	Self-report
Child focused			s		
	Eyberg Child Behavior Inventory (ECBI) [111]	36-item parent report of child conduct problems	Baseline	Families	Self-report
			3 months		
			6 months		
			12 months		
	Vanderbilt Assessment Scale Parent Version [112]	47-item assessment of core symptoms of DSM-IV diagnostic criteria (related to inattention, hyperactivity, oppositional behaviors, conduct problems, and anxiety depression) and impairment in performance	Baseline	Families	Self-report
			3 months		
			6 months		
			12 months		
	Dadds CU Scale [113]	20-item rating scale to assess psychopathic traits (narcissism, impulsivity, callousness-unemotionality) in children ages 6-13	Baseline	Families	Self-report
			3 months		
			6 months		
			12 months		
Parent focused					
	Public Health Questionnaire—9 [114]	10-item self-report to assess and monitor symptoms consistent with Major Depressive Disorder	Baseline	Families	Self-report
			3 months		
			6 months		
			12 months		
	Generalized Anxiety Disorder Scale—7 [115]	7-item self-report scale to screen and monitor symptoms consistent with Generalized Anxiety Disorder	Baseline	Families	Self-report
			3 months		
			6 months		
			12 months		
	Alabama Parenting Questionnaire [116]	Assessment of parenting practices yielding three subscales (Positive Parenting, Inconsistent Discipline, and Poor Supervision)	Baseline	Families	Self-report
			3 months		
			6 months		
			12 months		
Treatment participation					
	Barriers to Treatment Participation Scale [117]	44-item parent report of potential barriers to treatment participation	3 months	Families	Self-report
			6 months		
			12 months		
Treatment use and satisfaction	Therapy Attitude Inventory [118]	10-item, 5-point Likert-type parent report of satisfaction with process and outcome of therapy	3 months	Families	Self-report
			6 months		
			12 months		
	Multi-Sector Service Contacts—Revised Caregiver Form [119]	Report of additional services received by family/child in past 3 months and satisfaction with service(s)	Baseline	Families	Self-report
			3 months		
			6 months		
			12 months		

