Proctor and colleagues [72] have proposed a heuristic model that accounts for intervention strategies (EBT), implementation strategies (i.e., training models), and three distinct but interrelated set of outcomes within implementation research: implementation, service, and client outcomes. Using this taxonomy, we will use one intervention strategy (PCIT) to test three different training designs (LC, CM, DE) and will measure implementation and client outcomes to understand the conditions of transfer (generalization and maintenance). To understand the effectiveness of training methods, we will also measure training outcomes (outputs) articulated by Ford and Weissbein [71]. Measuring both implementation and client outcomes will help us to understand the success of the training condition for implementing an EBT in community settings [75]. Training outcomes (clinician level) are assessed using observational and self-report methods at four timepoints coinciding with the training schedule: baseline, 6 (mid), 12 (post), and 24 months (1 year follow-up). Immediately after clinician training began, parent–child dyads are recruited from the caseloads of participating clinicians. Client outcomes (parent–child dyad level) are assessed by parent report at four timepoints (pre-treatment, 1, 6, and 12 months after the pre-treatment). Implementation outcomes [75] (clinic level) are assessed using behavior observation, interview, and self-report measures with administrators, clinicians, and families at baseline, 6 (mid), 12 (post), and 24 months (1 year follow-up). This will include examining the overall penetration of the EBT (e.g., how extensively it is used) and whether the EBT is able to be diffused through the organization and sustained over the course of the study.

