### Aim 2: explore implementation outcomes, including acceptability, adoption, appropriateness, feasibility, fidelity, penetration, sustainability, and cost across training conditions

#### Analyses

Using the taxonomy of implementation outcomes defined by Proctor et al. [87], data will be collected on acceptability, adoption, appropriateness, feasibility, fidelity, penetration, and sustainability. We have four main hypotheses related to implementation outcomes. First, we hypothesize that rates of acceptability and appropriateness of PCIT will be high and equal across groups. Without doing a formal hypothesis test, we will examine the rates of acceptability and appropriateness. Second, we hypothesize that rates of adoption, fidelity, and feasibility will be the highest among the more active training conditions (LC, CM). As in Aim 1, we will compare these measures using a one-way ANOVA, with Bartholomew’s test for the ordered alternative. Third, we hypothesize that implementation costs will be lowest for the DE and highest for LC. We will compare the costs per clinician for the various treatments using ANOVA comparing the three once again. Measurement and analysis of cost will be supported by a consulting health economist. Finally, we hypothesize that participants in the LC will evidence greater penetration and sustainability of PCIT within the service settings. Because penetration is a proportion, we will first stabilize variances using the arcsin transform; we will then use one-way ANOVA as in Aim 1.

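### Table 2 describes penetration as an odds, but Aim 2 analyses it as a proportion with an arcsine transform that does not exist for an odds above 1

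*Protocol article*

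**What the plan says.** Two places in the protocol article fix this outcome.

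- **Table 2, Implementation outcomes, Penetration row.** Administrators complete the PCIT Learning Experience Feedback Form at 6, 12 and 24 months. The brief description gives, as an example of what is reported, "the number of consumers who receive PCIT divided by the number of consumers who were eligible to receive PCIT and did not receive it".
- **Aim 2, Analyses.** "Because penetration is a proportion, we will first stabilize variances using the arcsin transform", and "we will then use one-way ANOVA as in Aim 1". The hypothesis attached to the outcome is that "participants in the LC will evidence greater penetration and sustainability of PCIT within the service settings".

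The only other description, in Methods/design, is general: "examining the overall penetration of the EBT (e.g., how extensively it is used", with no formula. Nowhere does the article give a denominator of all eligible consumers or a step that turns the Table 2 ratio into a proportion.

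**The concern.** A proportion counts the treated in both numerator and denominator and lies between 0 and 1. The Table 2 ratio sets the treated against the untreated and runs from 0 upwards without limit. An arcsine transform, with or without the usual square root, exists only up to 1. The measure as described and the analysis as described therefore do not fit each other.

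Penetration carries part of the fourth Aim 2 hypothesis. Followed literally, the plan gives no analysable value for the clinics with the highest uptake, and it gives the remaining clinics unequal variances on a scale chosen to equalize them.

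**Working it through.** The article states no sample size, power or expected rate for penetration, so there is no figure of its own to reproduce. The check is algebra on the two statements.

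**Inputs.** The ratio comes from Table 2; the scale, transform and test come from Aim 2. The values of p below, and the 50 eligible consumers per clinic used in the simulation, are assumptions chosen to show the range.

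**Step 1: what the ratio is.** Let a consumers receive PCIT and b be eligible but not receive it, with n = a + b and p = a/n. The Table 2 ratio is r = a/b = p/(1-p).

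**Step 2: where the transform exists.** arcsin(√r) and arcsin(r) both need r ≤ 1. Since p/(1-p) ≤ 1 is the same as p ≤ 0.5, the transform fails exactly when p exceeds 0.5. At p = 1 the ratio divides by zero.

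**Step 3: whether variance is stabilized below 0.5.** Start from Var(p̂) = p(1-p)/n and use the delta method.

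- For arcsin(√p): 4n·Var = 1 at every p.
- For arcsin(√r): dr/dp = 1/(1-p)², the squared slope of arcsin(√r) is 1/[4r(1-r)], and r(1-r) = p(1-2p)/(1-p)². Multiplying through gives 4n·Var = 1/[(1-p)(1-2p)].
- Example at p = 0.4: 1/(0.6 × 0.2) = 8.33.

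| Share treated p | Ratio r | arcsin(√r) | 4n·Var on r | arcsin(√p) |
|---|---|---|---|---|
| 0.1 | 0.111 | 0.340 | 1.39 | 0.322 |
| 0.2 | 0.250 | 0.524 | 2.08 | 0.464 |
| 0.3 | 0.429 | 0.714 | 3.57 | 0.580 |
| 0.4 | 0.667 | 0.955 | 8.33 | 0.685 |
| 0.5 | 1.000 | 1.571 (upper limit) | no finite value | 0.785 |
| 0.51 | 1.041 | undefined | undefined | 0.795 |
| 0.6 | 1.500 | undefined | undefined | 0.886 |
| 0.8 | 4.000 | undefined | undefined | 1.107 |
| 1.0 | divides by zero | undefined | undefined | 1.571 |

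**Step 4: simulation.** With 50 eligible consumers per clinic, the chance that a clinic's observed ratio exceeds 1 is about 0.1% at a true p of 0.3, 6% at 0.4 and 44% at 0.5. Among the defined values, 4n·Var on r is 1.56, 2.25, 4.25 and 8.82 at p = 0.1, 0.2, 0.3 and 0.4, in line with the delta method.

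**Step 5: after correction.** On a/(a+b), the transform is defined at every p from 0 to 1. Simulated 4n·Var stays between 1.02 and 1.13 for p from 0.1 to 0.5, so the planned transform does its job.

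**The case against.** The strongest reply is that the Table 2 text is only an illustration in a brief-description column, that the form itself is not shown, and that Aim 2 says outright that penetration is a proportion. A slip in one table cell, with a proportion intended throughout, is a fair reading. This stands as far as it goes: the article does not show that the stored data are odds. It does not remove the point, because the cell holds the only formula in the article and nothing corrects it.

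A reader might infer more, and the documents do not support it:

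- **That the best clinics will be lost and the comparison biased against LC.** No expected penetration is given. If uptake is low everywhere, all values remain defined, and below 50% the ratio keeps clinics in the same order. It also widens differences there: 30% versus 40% becomes 0.43 versus 0.67. A failed transform would be visible to the analyst, and the article plans initial checks of unusual observations and missing-data patterns, and sensitivity analysis for missing data.
- **That the arcsine ANOVA must be dropped.** With the corrected denominator it behaves as intended. Replacing it is a preference.
- **That clustering and binomial models are ignored.** The Aim 1, Proposed statistical analyses and Nesting sections bring in nesting, possible random effects for clinic, and logistic regression where suitable. County is absent from the model shown under Nesting, but that concerns the whole trial and does not follow from the penetration definition.

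**Conclusion.** The point holds as an incompatibility between two statements in the current text. It is wrong as written; it is not a detail left to a fuller document, because both the formula and the transform are stated. The 50% threshold and the division by zero at 100% are exact and rest on no assumption beyond the literal Table 2 ratio. The loss of variance stabilization below 50% is a delta-method result, supported by simulation at an assumed 50 eligible consumers per clinic.

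The practical size is unknown. It depends on how many clinics exceed or come near 50%, and on whether the form holds two counts or a single ratio. If both counts are kept, no data are lost and the error is fully correctable. Bias in the LC comparison is possible only if high-uptake clinics were dropped or truncated and were unevenly spread across conditions. The article establishes neither.

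**What to change.** 1. In Table 2, define penetration as received PCIT / (received + eligible but not received).
2. Confirm that the form stores both counts. If only the ratio r was kept, recover the proportion as r/(1+r) and treat a zero denominator as 100%, after checking that the clinic did treat at least one consumer.
3. In Aim 2, state that the arcsine transform and the nested ANOVA are applied to that proportion.

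Optionally, a binomial (logistic) model on the two counts, which the Proposed statistical analyses section already leaves room for, would weight clinics by their number of eligible consumers. It needs both counts and is not required to cure the inconsistency.

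The cost is a wording change in two places and a recomputation, with no new data collection if the counts are stored. If only ratios were stored, the proportion can still be recovered, but the number of eligible consumers per clinic cannot.
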